## Discussion

This trial is the first to test smartphone app-based mindfulness training to for smoking cessation. Although many meditation-related smartphone apps are available, very few have been tested for use in clinical groups such as smokers [18]. In addition, there are currently few smoking cessation interventions that target the association between craving and smoking [12]. In-person mindfulness training has been found to improve smoking cessation rates and decrease the association between craving and smoking [14]. Therefore, this trial will test whether mobile mindfulness training is associated with similar outcomes.

The choice of a control group for this trial was critical for isolating and testing variables of interest, by comparing mobile mindfulness training to experience sampling-only. Alternative comparators could be in-person mindfulness training, an online smoking cessation program, waitlist control, or another smartphone-based smoking cessation intervention. However, there is limited evidence for the efficacy of existing smartphone apps for smoking cessation, and other apps offer additional features not available in the tested intervention that introduce confounds, or vice versa. Experience sampling may bring awareness to smoking, craving, and mood, similar to mindfulness training, therefore experience sampling-only was chosen as the control, to disentangle the effects of mindfulness training from those of effective self-monitoring. Exploratory analyses will test whether experience sampling-only also leads to mindfulness, and whether increases in mindfulness are associated with smoking cessation.

If the intervention is found to be effective, this RCT will provide a platform for large-scale clinical trials to compare mobile mindfulness training to active behavioral treatments for smoking cessation, and to disseminate this treatment to the wider community.

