**Methods/Design:**

A two-group parallel-randomized clinical trial with allocation concealment will be conducted. Group assignment will be concealed from study researchers through to follow-up. The study will be conducted by smartphone and online. Daily smokers who are interested in quitting smoking and own a smartphone (*n* = 140) will be recruited through study advertisements posted online. After completion of a baseline survey, participants will be allocated randomly to the control or intervention group. Participants in both groups will receive a 22-day smartphone-based treatment program for smoking. Participants in the intervention group will receive mobile mindfulness training plus experience sampling. Participants in the control group will receive experience sampling-only. The primary outcome measure will be one-week point prevalence abstinence from smoking (at 6-months follow-up) assessed using carbon monoxide breath monitoring, which will be validated through smartphone-based video chat.

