### Participants

Participants will be eligible if they are: age 18–65 years; smoke at least 5 cigarettes per day; less than 3 months abstinence in the past year; own an iPhone (https://www.apple.com/iphone/) or Android (https://www.android.com/intl/en_us/); and are motivated to quit, as indicated by a score of at least 9 of 10 on the Contemplation Ladder [28], and at least 4 of 5 on one item of the Action subscale of the Readiness to Change Questionnaire [29]. “I am trying to smoke less than I used to” from 1=Strongly disagree to 5=Strongly agree” ”. If smartphone ownership is found to be a barrier to recruitment, smartphones and/or voice/data plans will be provided.

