### Recruitment and randomization

All study procedures will be automated using Yale Qualtrics Survey Tool. The study website links to a short screening survey. The survey notifies an individual if they are eligible or not eligible. If eligible, they are asked for their contact information and directed to an online consent form, which includes study contact information to ask questions. Those who provide consent are sent an email with a link to the baseline survey and a copy of the consent form. This email also includes a recommendation for nicotine replacement therapy or other pharmacotherapies [19]. At the end of the baseline survey, participants are randomized to treatment group and emailed a link to download their app and begin the study.

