#### Control group

The control group will receive experience sampling-only, to control for: (i) expectancy effects of treatment for smoking; (ii) non-specific effects of using a smartphone for smoking cessation; and (iii) potential effects of experience sampling for smoking cessation. Experience sampling may bring awareness to craving and smoking, and is similar to other interventions that teach individuals to identify triggers and track the number of cigarettes they smoke. Experience sampling-only will be delivered by smartphone app for 22 days. An introductory email will explain that the app will help individuals self-monitor their smoking habits, recognize when and how often the smoke, and identify triggers for smoking. Upon downloading the app, participants will input the number of cigarettes smoked per day and set a quit date of 3 weeks from today. They will view a tutorial explaining the app features and begin the first day. Across treatment, experience sampling procedures will be matched to the intervention group. From day 22, all study procedures will be matched to the intervention group. In addition, along with study payment at 6-months, this group will receive a free download code for the treatment app.

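### The plan promises to test whether experience sampling alone leads to mindfulness, but both arms receive it, so only uncontrolled change can be described

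*Protocol article*

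**What the plan says.** The abstract (Methods/Design) sets out two randomised arms: "Participants in the intervention group will receive mobile mindfulness training plus experience sampling", and "Participants in the control group will receive experience sampling-only". The Control group section adds: "Across treatment, experience sampling procedures will be matched to the intervention group". The Discussion gives the reason for this comparator: "experience sampling-only was chosen as the control, to disentangle the effects of mindfulness training from those of effective self-monitoring". It then adds an exploratory objective: "Exploratory analyses will test whether experience sampling-only also leads to mindfulness, and whether increases in mindfulness are associated with smoking cessation".

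Mindfulness is measured in two ways. The Exploratory outcomes section lists a 24-item mindfulness questionnaire at baseline and at 1, 3 and 6 months. The Secondary outcomes section lists mindfulness as captured by the app, through the check-in items described under Intervention group (six prompts a day for 22 days).

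**The concern.** The comparator was chosen so that sampling would be held constant between arms. That choice isolates mindfulness training, and it is also why the trial cannot estimate what sampling itself does. The exploratory objective nevertheless uses a causal verb and promises a test. Followed as written, a rise in control-arm mindfulness could be reported as an effect of sampling when no group without sampling exists to show what would have happened otherwise. An analysis plan can choose a model, but it cannot supply the missing comparator.

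**Working it through.** The plan gives no power or precision figure for this question, so there is none of its own to reproduce. The check is structural, followed by one illustration.

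**1. What the randomised contrast identifies.** Write ES for experience sampling and MT for mindfulness training.

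| Arm | Components |
|---|---|
| Intervention | MT + ES |
| Control | ES |

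Difference: (MT + ES) − (ES) = MT, given ES. The ES term cancels. By schedule each arm is offered 6 × 22 = 132 prompts, so the between-arm difference in prompts is 132 − 132 = 0.

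**2. What other evidence the plan collects.**

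- *Questionnaire.* The baseline survey comes before the app is downloaded (Recruitment and randomization), so a before-after change exists in the control arm. It has no concurrent comparison without sampling.
- *In-app items.* These give a repeated series in the control arm over 22 days. They are collected by the sampling itself, so no value exists from before sampling started.
- *Completed check-ins.* The schedule is fixed but completion varies: the plan expects an 80% response and excludes days with fewer than 3 check-ins. Completion could be related to mindfulness within the control arm, but it is chosen by the participant, so the relation would be observational.

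**3. What else moves over the same period in the control arm.**

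- Time and repeated completion of the same instruments.
- Pharmacotherapy. Of the message sent after consent, the Recruitment and randomization section says: "This email also includes a recommendation for nicotine replacement therapy or other pharmacotherapies".
- The quit attempt. Participants set a quit date 3 weeks after starting, that is day 21 or 22. The 1-month survey falls at about day 30, so 30 − 22 = 8 to 30 − 21 = 9 days after the quit date. All the follow-up surveys come after it. Most of the in-app series comes before it, so this confounder applies mainly to the questionnaire.

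**4. Illustration of the consequence.** Suppose sampling has no effect, and other causes shift the mean by d, in units of the SD of change. For a two-sided pre-post test at 0.05 with n in the arm, the probability of significance is

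Φ(d√n − 1.96) + Φ(−d√n − 1.96).

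Take n = 59 (the analysed group size in the Sample size section) and n = 70 (half of 140 recruited). The values of d are assumptions, since the document gives none.

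| d (assumed) | n = 59 | n = 70 |
|---|---|---|
| 0 | 5% | 5% |
| 0.1 | 12% | 13% |
| 0.2 | 34% | 39% |
| 0.3 | 64% | 71% |

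For d = 0.2 and n = 59: 0.2 × √59 = 1.536. Then Φ(1.536 − 1.96) = Φ(−0.424) ≈ 0.336, and the second term is negligible. A significant pre-post result is therefore weak evidence for a sampling effect, and nothing in the design limits how often it arises from other causes.

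**The case against.** The strongest reply is that experience sampling-only is also the name of the control group. The sentence may then ask only whether that group's mindfulness rises too, which the baseline and follow-up questionnaires can answer. The clause sits in the Discussion, is called exploratory, and is not among the aims and hypotheses in the Background. No method is attached to it, and a condensed article commonly leaves such detail to a fuller document. Much of this stands. It is why the point is small and why a change of wording is enough. It does not rescue the sentence, because a test of whether something leads to mindfulness reads as causal and no further detail can create a group without sampling.

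A second reply is that the plan holds more than the questionnaire. That is correct. A reader might infer that the control-arm questionnaire change is the only evidence available, but the in-app items and the variation in completed check-ins also exist, and most of the in-app series precedes the quit date. Neither source identifies a causal effect: the first lacks a reading from before sampling, and the second is not randomised.

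A third is that the drift values in the illustration are not from the document. They are assumptions, and the argument does not depend on them.

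**Conclusion.** The point holds as a minor one. With matched sampling in both arms and none without it, a causal effect of sampling on mindfulness is not identified, and the evidence on it is uncontrolled or observational. This rests on the design as described, not on any numerical assumption. The 12% to 71% range in the illustration rests on assumed drifts of 0.1 to 0.3 SD of change with no true sampling effect.

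Two stronger readings are not supported. A reader might infer that a rise in control-arm mindfulness will be used to explain away a null primary result. The Discussion does remark that sampling may raise awareness much as mindfulness training does, but nowhere says that a null result would be interpreted that way. A reader might also infer that the trial's main conclusions are compromised. They are not: the primary abstinence comparison and the secondary comparisons are unaffected. The second half of the quoted sentence asks only for an association between mindfulness and cessation, so it is unaffected as well.

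**What to change.** Reword the exploratory objective so that it describes the control arm's change in mindfulness from baseline, with an estimate and confidence interval, and says that the change is not attributed to sampling. Base any inferential statement about mindfulness on the randomised between-arm difference in the questionnaire, adjusted for its baseline value. That difference answers what mindfulness training adds to sampling, and should be labelled so. If completed check-ins are related to mindfulness, call that analysis observational. No advance commitment about how to interpret a null primary result is needed.

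The cost is one reworded sentence and one baseline-adjusted comparison on data already collected. The trial gives up a causal statement about experience sampling, which would need an arm without it.
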